### Breaking of the study blind

#### On study

If an adverse event is regarded as a potential Serious Unexpected Suspected Adverse Reaction (SUSAR) by the sponsor the treatment group to which the trial subject affected belongs will be unblinded for that subject alone. The procedure will ensure that the identity of the investigational medicinal product (IMP) is only revealed as far as necessary (GCP Directive). All staff will have received training on all aspects of the trial protocol prior to commencement of the trial.

The principal investigator (PI) or authorised member of the team will have a written procedure for requesting randomisation codes for rapidly identifying a blinded IMP in an emergency. Breaking the blind of a trial subject will be at the discretion of the PI, when clinically indicated for the safety of the patient, or in the event of a SUSAR. If the patient needs to be unblinded we will refer to the unblinding SOP for complete details of the procedures to be followed. The master randomisation codes will be kept by the clinical trial Pharmacist and the PI. Unblinding will be performed by the senior clinician/pharmacist when the criteria for a Serious Adverse Event (SAE/SUSAR) have been met and there is a necessity for the PI or treating healthcare professional to know which treatment the patient is receiving to ensure that the patient receives appropriate urgent safety measures.

A 24-hour contact number will be available in the circumstances when unblinding is required. The scenario will be communicated and when the unblinding criteria are met the unblinding will ensue. The PI will document the breaking of the code, and the reasons for doing so, in the site file and in the patient’s medical notes, and in accordance with the clinical trial protocol. If at the EOT visit a clinical failure is apparent and the addition of phenoxymethylpenicillin is felt to be clinically necessary, code breaking will be made possible on a 24-hour basis by making contact with the PI. It is felt that unblinding will be an extremely unlikely event as a treatment failure will more than likely require intravenous antibiotics. Any compromises in blinding will be reported in the trial conclusion.

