##### Microbiological assay

Whenever possible a specimen for culture and sensitivity will be taken from the infection site at enrolment. This may be from blister fluid or exudate. Specimen results will be made available at follow-up to guide appropriate therapy. Blood cultures will not be taken in this study. Since the expected microbiological yield will be low, a test of microbiological cure will not be used in this study.

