##### Follow-up

Patients will be telephoned at 3 to 5 days by a study investigator to encourage treatment compliance and EOT visit follow-up. Any deterioration in patient symptoms may be addressed at this visit and a return for clinical assessment may be recommended. The patient will be reviewed at 7 to 10 days after treatment commencement (EOT visit) in the enrolment centre and the area of infection will be measured. At this visit, the patient will be given an SF-36 and ESTI score to complete. A final TOC visit or telephone call will be arranged for 30 days after the enrolment of the patient into the trial.

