#### Outcome measures

##### Primary outcome

The primary outcome measure under study is the proportion of patients treated in each group in which there is greater than or equal to a 50% reduction in the maximal diameter of erythema from the area measured at enrolment to that at the end-of-treatment visit (7 to 10 days).

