##### Measurement of the primary outcome

Clinical cure: Reduction in the area of cellulitis by ≥50% of the initial diameter.

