##### Secondary outcomes

•Clinical failure: a failure of the initial maximal diameter of infection to reduce by ≥50%

•Clinical relapse: initial improvement in cellulitis at the EOT visit followed by a worsening or re-appearance of cellulitis at the TOC visit.

•Quality of life: the SF-36 and the ESTI score at the EOT visit will be measured.

•Compliance with therapy: the number of unused study medications counted at the EOT visit will be measured.

•Adverse Events: all adverse events will be recorded and submitted to the Irish Medicines Board and the Research and Ethics Committee.

•Microbiological profile: the results of specimens sent for culture to receiving laboratories will be profiled.

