#### Data analysis

Both intention-to-treat (ITT) and per-protocol analysis will be performed. ITT analyses include all patients randomised to the trial regardless of whether they satisfied entry requirements, received the assigned treatments, withdrew from the trial or adhered to the protocol. Missing values will be imputed using a suitable imputation method (last value carried forward or mixed model). A per-protocol analysis includes only patients who completed the full course of treatment and adhered to the protocol requirements. In a non-inferiority trial setting a per-protocol analysis may be more appropriate since it is more likely to reflect actual differences between the two treatments. Furthermore, ITT analysis may be interpreted as being too liberal in a non-inferiority trial and may bias toward making the two treatments appear similar
[24]. As a result, both an ITT and per-protocol analysis will be performed on the resulting data to assess non-inferiority of the placebo/flucloxacillin combination. In particular, to declare non-inferiority, both ITT and per protocol analysis should exclude the non-inferiority margin.

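### Patients switched for lack of response before the end-of-treatment visit can count as ITT cures and are dropped from the per-protocol set, so requiring both analyses does not reliably hold the 2.5% error rate

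*Protocol article*

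**What the plan says.** All references are to the protocol article.

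- **Endpoint.** Primary outcome requires "greater than or equal to a 50% reduction in the maximal diameter of erythema from the area measured at enrolment", assessed at the day 7 to 10 visit. Measurement of the primary outcome gives "Clinical cure: Reduction in the area of cellulitis by ≥50% of the initial diameter". Secondary outcomes defines the converse: "Clinical failure: a failure of the initial maximal diameter of infection to reduce by ≥50" per cent. None of the three mentions other antibiotics, intravenous therapy or admission.
- **Contact during treatment.** Follow-up describes a telephone call at 3 to 5 days, within the 7-day course: "Any deterioration in patient symptoms may be addressed at this visit and a return for clinical assessment may be recommended". Microbiological assay adds: "Specimen results will be made available at follow-up to guide appropriate therapy".
- **Analysis sets.** Data analysis says "ITT analyses include all patients randomised to the trial regardless of whether they satisfied entry requirements, received the assigned treatments, withdrew from the trial"; non-adherence is no ground for exclusion from this set either. For the other set: "A per-protocol analysis includes only patients who completed the full course of treatment and adhered to the protocol requirements".
- **Decision rule.** Data analysis warns that ITT can make the arms look alike, suggests that per-protocol may be the more appropriate analysis, and requires both to exclude the 12.5-point margin.

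**The concern.** A patient who does not respond to study drug and is given something else before EOT is a failure of the assigned treatment. Under the printed rules, neither analysis is sure to record that.

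- **ITT** reads the diameter at EOT whatever produced it. If the replacement treatment has halved the lesion, the patient is a cure for the assigned arm.
- **Per-protocol** removes the patient for not completing the course. When the reason is lack of response, the set is selected on the outcome.

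The arm with more true failures has more patients recoded or removed, so the observed difference shrinks. In this trial a smaller difference favours the hypothesis under test. The per-protocol analysis is meant to correct the tendency of ITT to blur differences, but here it can err in the same direction. What is at stake is the error rate of the primary non-inferiority claim.

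**Working it through.** **Inputs from Sample size, power and statistical methods:** success 85% on dual therapy, margin 12.5 points, one-sided α = 0.025, power 90%, 172 per arm.

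**The plan's own figure.** n = 2 × 0.85 × 0.15 × (1.960 + 1.282)² / 0.125² = 171.5, rounded up to 172. The plan's number is reproduced; power at 172 is 90.1%.

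**Assumptions not in the documents.** A share s of study-drug failures is switched for lack of response before EOT. A share h of those has halved in diameter by EOT. Both shares are the same in the two arms. Truth is set at the margin: p = 0.85 for dual therapy and p = 0.725 for monotherapy, on study drug alone.

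**Expected success under the printed rules**

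- ITT: p + (1 − p) × s × h
- Per-protocol: p / [1 − (1 − p) × s]

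**Worked case, s = 0.5 and h = 0.5**

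- ITT, dual: 0.85 + 0.15 × 0.25 = 0.8875
- ITT, monotherapy: 0.725 + 0.275 × 0.25 = 0.79375
- ITT difference: 9.4 points
- Per-protocol, dual: 0.85 / 0.925 = 0.919
- Per-protocol, monotherapy: 0.725 / 0.8625 = 0.841
- Per-protocol difference: 7.8 points

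The true difference is 12.5 points.

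**False non-inferiority, by simulation.** 172 per arm, unpooled one-sided 97.5% upper limit compared with 12.5 points, at least 400,000 trials per case:

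| Failures switched (s) | Of those, halved by EOT (h) | ITT difference (points) | PP difference (points) | False non-inferiority, both required |
|---|---|---|---|---|
| 0% | – | 12.5 | 12.5 | 2.6% |
| 10% | 0% | 12.5 | 11.7 | 2.3% |
| 10% | 50% | 11.9 | 11.7 | 3.0% |
| 25% | 0% | 12.5 | 10.5 | 2.3% |
| 25% | 25% | 11.7 | 10.5 | 3.3% |
| 25% | 50% | 10.9 | 10.5 | 4.7% |
| 25% | 100% | 9.4 | 10.5 | 7.5% |
| 50% | 0% | 12.5 | 7.8 | 2.4% |
| 50% | 25% | 10.9 | 7.8 | 5.4% |
| 50% | 50% | 9.4 | 7.8 | 11% |
| 50% | 100% | 6.3 | 7.8 | 25% |

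Per-protocol alone errs in about 7.5% of trials at s = 25% and 26% at s = 50%, whatever h is. If switched patients are counted as failures and kept in both analyses, the rate is 2.6% in every row, which is the ordinary small excess of this interval over 2.5%.

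**The case against.** **Do failures leave both analyses?** A reader might infer this, and the documents do not support it. ITT keeps everyone randomised. A switched patient whose lesion has not halved remains an ITT failure. A switched patient with no EOT measurement is also a failure under last value carried forward, because enrolment is the only earlier planned measurement; the mixed-model option does not guarantee this. Only switched patients who have halved by EOT are recoded as cures.

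**Does the protocol expect early switching?** It permits it. Follow-up allows reassessment after the call and does not mention a switch. Culture results become available at an undated follow-up, and the yield is expected to be low. The remark under Breaking of the study blind that "a treatment failure will more than likely require intravenous antibiotics" might be read as evidence of early switching. It concerns failure found at the EOT visit, when the endpoint is read, and is no such evidence. Entry is limited to Eron Class I and II disease treatable orally, so switching may be uncommon.

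**Does the two-analysis rule never protect?** That is also too strong. After a day 3 to 5 call only about 2 to 7 days remain (7 − 5 to 10 − 3) for a worsening lesion to halve in diameter. If none does, ITT holds the joint error at about 2.3 to 2.4%, even where per-protocol alone errs 26% of the time.

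**Is this left to the SAP?** A SAP could refine what adherence means. But the endpoint and the full-course condition are fixed in the article and give this result if followed as written. A SAP that counted switching as failure would have to change them.

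What stands of the objection: the size is unknown, early switching is a possibility rather than a stated expectation, and ITT gives partial protection.

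**Conclusion.** The point holds as a conditional one and should be fixed. The size-only endpoint and the full-course per-protocol set together allow a true failure of study drug to be a cure in one analysis and absent from the other.

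The direction towards non-inferiority rests on two conditions: monotherapy truly fails more often, and failures are switched at similar rates in both arms. Under these, per-protocol is biased whenever failures are switched, and ITT is biased to the extent that switched patients respond by EOT.

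Joint false non-inferiority runs from about the nominal 2.5% (few switched, or none responding) through 3% and 4.7% to 11% (half switched, half of those responding), and 25% if half are switched and all respond. The documents do not say where in this range the trial would fall, so no single figure should be presented as the expected error. That uncertainty is why this is not a must-fix.

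**What to change.** These changes affect how patients are counted, not how they are treated.

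1. **Primary outcome, Measurement of the primary outcome and Secondary outcomes.** Count as a clinical failure, whatever the diameter, any patient who on or before the EOT visit receives a non-study systemic antibiotic for the index infection, or is admitted for it, because of inadequate response or worsening. Record the reason blinded to allocation.
2. **Data analysis.** Keep patients who stop or switch for inadequate response in the per-protocol set as failures. Exclude early stoppers only for reasons unrelated to response.
3. **Switches for intolerance.** State one rule for how these count in ITT and in per-protocol. Counting every switch as failure in the primary analysis would not be neutral: if dual therapy were less well tolerated (an assumption), it would add comparator failures and itself favour non-inferiority.
4. **Sensitivity analysis.** Report one in which any switch, for any reason, counts as failure.

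**Cost.** A few sentences and one proforma item (new antibiotic or admission, with date and reason). The observed success rate may be slightly lower. The sample size stays at 172 per arm if the 85% means success on study drug alone; if it was meant to include rescued patients, that planning rate needs another look. Trial status says that enrolment has not begun, so the change can be made before any data exist.

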##### Therapeutic intervention

Once enrolled patients will be given a 7-day course of either oral flucloxacillin 500 mg four times daily and oral phenoxymethylpenicillin 500 mg four times daily or oral flucloxacillin 500 mg four times daily and oral placebo four times daily.

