### Sample size, power and statistical methods

Non-inferiority of oral flucloxacillin and placebo relative to oral flucloxacillin and phenoxymethylpenicillin for the above primary and secondary outcomes will be assessed. Sample size per treatment arm is calculated according to an assumed treatment success rate of 85% with oral flucloxacillin and phenoxymethylpenicillin, an equivalence threshold Δ = 12.5% and an α = 0.025 (as this is a non-inferiority study). Sample sizes were calculated using PASS statistical software (Hintze J.(2008) PASS 2008. NCSS, LLC, Kaysville, Utah, USA http://www.ncss.com). Given the preferred study power of 90% for non-inferiority trials, a minimum sample size of 172 in each treatment group is required (n = 344). Non-inferiority will be assessed using a one-sided confidence interval (CI) on the difference of proportions between the two groups. If the upper limit of the CI is less than the equivalence threshold of 12.5%, then non-inferiority is inferred.

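### The per-protocol set that must also succeed admits only full-course completers, with no stated tolerance, and the sample size has no room for the patients this removes

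*Protocol article*

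**What the plan says.** Under Data analysis, the protocol article defines the set: "A per-protocol analysis includes only patients who completed the full course of treatment and adhered to the protocol requirements". The same section gives it a deciding role: "to declare non-inferiority, both ITT and per protocol analysis should exclude the non-inferiority margin". ITT is defined broadly: "ITT analyses include all patients randomised to the trial regardless of whether they satisfied entry requirements, received the assigned treatments", and it also covers those who withdrew or did not adhere. The section adds that per-protocol may be the more suitable analysis in a non-inferiority trial.

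Under Therapeutic intervention, the course lasts 7 days. One arm takes flucloxacillin with phenoxymethylpenicillin, each four times daily. The other takes "oral flucloxacillin 500 mg four times daily and oral placebo four times daily". Under Secondary outcomes, compliance is a pill count: "the number of unused study medications counted at the EOT visit will be measured".

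The sample size section assumes "an assumed treatment success rate of 85% with oral flucloxacillin and phenoxymethylpenicillin", with a margin of 12.5 points, alpha 0.025 and 90% power. It arrives at a minimum of 172 per arm. The section on patient randomisation creates two groups of that same size, 344 in total.

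**The concern.** The per-protocol definition is a stated rule, not a gap. It names full-course completion as a condition of entry and gives no minimum share of doses and no exception for any reason for stopping. Two consequences follow.

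First, the set is selected on what patients do after randomisation. Those who stop because of side effects, or because the lesion has cleared, leave the comparison. Only one arm receives the second active antibiotic, so stops for side effects could differ between arms, although the documents give no rates that would show this.

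Second, the set must pass the same test as ITT, but the trial is sized as if nobody were excluded. At stake is a failed claim for a regimen that is truly equivalent, because too few patients remain in one of the two required analyses.

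**Working it through.** **Inputs.** From the sample size section: 85% success with dual therapy (taken as equal in both arms), margin 0.125, one-sided alpha 0.025, power 90%, 172 per arm. From Therapeutic intervention: 7 days × 4 = 28 dosing times of two products, or 56 units. Assumed, because the documents give none: the share excluded, the miss rate per dosing time, and how far misses cluster within patients.

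**1. The plan's own figure.** n per arm = (1.960 + 1.282)² × 2 × 0.85 × 0.15 / 0.125² = 171.5, rounded up to 172. This reproduces exactly.

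**2. Power of the per-protocol test against the share excluded.** Power = Φ(0.125 / √(2 × 0.85 × 0.15 / n) − 1.960). Patient numbers are rounded down. The last column is the exact binomial power of the rule that the upper 97.5% limit (unpooled) lies below 12.5 points.

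| Excluded (assumed) | n per arm | Standard error | Normal power | Exact power |
|---|---|---|---|---|
| 0% | 172 | 0.0385 | 90.1% | 90.1% |
| 10% | 154 | 0.0407 | 86.7% | 86.7% |
| 20% | 137 | 0.0431 | 82.6% | 82.6% |
| 30% | 120 | 0.0461 | 77.4% | 77.5% |

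The power for both analyses to succeed cannot exceed the per-protocol figure.

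**3. What the every-dose reading would imply.** If a patient must take all 28 dosing times and misses are independent with probability m, the share retained is (1 − m)^28. If misses cluster within patients, a beta-binomial model gives B(a, b + 28) / B(a, b), where a = m(1 − ρ)/ρ, b = (1 − m)(1 − ρ)/ρ and ρ is the within-patient correlation. For m = 0.02 and ρ = 0.1, a = 0.18 and b = 8.82, and 77% are retained. Power is exact, as in step 2.

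| Miss rate m | Retained, independent | Power | Retained, ρ = 0.1 to 0.5 | Power |
|---|---|---|---|---|
| 1% | 75% (129 per arm) | 81% | 88–96% | 86–89% |
| 2% | 57% (97 per arm) | 68% | 77–92% | 81–87% |
| 5% | 24% (40 per arm) | 36% | 51–82% | 65–84% |

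The result depends heavily on clustering. Independence is the harsher model, because it spreads the same misses over more patients.

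**4. What an exposure rule would change.** At least 80% of 28 is 22.4, so 23 or more doses, which allows five misses. Under independence more than 99% qualify at all three miss rates. With clustering and a 5% miss rate, 91–94% qualify. A patient who stops after day 5 has taken 20/28 = 71% and is still excluded.

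**The case against.** The strongest reply is that the article never says every dose. Completing the course could simply mean not stopping before day 7. The pill count is listed as a compliance outcome and is not tied to membership of the set. A reader might infer that one leftover capsule excludes a patient. That is the literal reading but not the only one, and the documents do not settle it. What survives is that early stoppers are excluded on either reading.

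A reader might also infer that the set will be small. The documents give no non-completion rate, so this cannot be shown. The worst figures above need both the every-dose reading and independent misses.

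A third tempting inference is that non-inferiority could be claimed on exceptional adherers alone. The article rules this out, because ITT on all randomised patients must also exclude the margin. Both arms also take a second tablet four times daily under blinding, so ordinary missed doses have no evident reason to differ by arm.

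Finally, adherence cut-offs and deviation lists usually belong in the analysis plan, and the article says that plan will be agreed before unblinding. This is fair for details left open. Here a definition has been published, and a later threshold would amend it, which is the change requested. The choice of 80% is only an example; nothing in the documents favours it over another threshold.

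**Conclusion.** The point holds in limited form. A required analysis is restricted to full-course completers without tolerance, which selects on post-randomisation behaviour, and the planned number has no allowance for it. With equal true rates of 85%, power in that analysis falls from 90.1% to 86.7%, 82.6% or 77.5% if 10%, 20% or 30% are excluded. The loss is modest at 10% and substantial by 30%. Which of these applies cannot be known from the documents. Under the every-dose reading and an assumed 2% miss rate, power is 68% with independent misses and about 81–87% with clustering at assumed correlations of 0.1 to 0.5. The definition should be changed, but the conclusion of the trial would still have ITT as a second safeguard.

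**What to change.** Before unblinding, replace the full-course condition with a stated minimum exposure taken from the pill count already planned, for example at least 80% of scheduled doses of each of the two products. List the protocol deviations that exclude a patient. Report exclusions by arm and reason. Keep the full-completion set as a sensitivity analysis.

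An exposure rule does not by itself retain early stoppers, as the day-5 example shows. The definition should therefore also say how patients who stop for adverse events or early resolution are classified in the analysis.

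The cost is a few sentences in the analysis-set definition and one table. The article's trial status section says that enrolment still awaits funding, so no data are affected. The small downside is that patients with a few missed doses stay in the per-protocol set.

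### The per-protocol set is restricted to patients who completed the course, yet compliance and adverse events fall under the same both-sets non-inferiority rule; limit that rule to efficacy outcomes (minor)

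*Protocol article*

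**What the plan says.** Four statements in the protocol article have to be read together.

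- **Outcomes.** Secondary outcomes lists "Compliance with therapy: the number of unused study medications counted at the EOT visit will be measured" and also "Adverse Events: all adverse events will be recorded and submitted to the Irish Medicines Board and the Research and Ethics Committee".
- **Scope of the non-inferiority assessment.** Sample size, power and statistical methods says that non-inferiority of monotherapy "for the above primary and secondary outcomes will be assessed". The one margin given there is 12.5 percentage points on a difference of proportions, with a one-sided interval and an α of 0.025.
- **Analysis sets.** Data analysis says that "both an ITT and per-protocol analysis will be performed on the resulting data to assess non-inferiority of the placebo/flucloxacillin combination". On the ITT side, "ITT analyses include all patients randomised to the trial regardless of whether they satisfied entry requirements, received the assigned treatments, withdrew from the trial". On the other side, "A per-protocol analysis includes only patients who completed the full course of treatment and adhered to the protocol requirements".
- **Decision rule.** In the same section: "to declare non-inferiority, both ITT and per protocol analysis should exclude the non-inferiority margin".

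Neither section limits the per-protocol analysis to efficacy, and neither exempts compliance or adverse events from it.

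**The concern.** A per-protocol set is there to protect an efficacy comparison from dilution by patients who did not take the treatment. Data analysis gives that reason itself: ITT may make the two arms look more alike than they are. The reason does not carry over to compliance or adverse events. There, completing the course is the outcome itself (compliance) or is affected by it (adverse events), so selecting on completion means selecting on what is being compared.

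The Background (Measures of severity) names efficacy, tolerability and compliance as the comparison of interest. Two of those three would therefore get a per-protocol result that is either empty or biased. Data analysis also tells the reader that the per-protocol analysis may be the more appropriate one, which gives that result more weight than it deserves for these two outcomes.

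**Working it through.** **Plan's own figure.** The sample size reproduces and is not in question. With 85% success in both arms (the article states it for dual therapy; the same rate on monotherapy is assumed), n = 2 × 0.85 × 0.15 × (1.960 + 1.282)² / 0.125² = 171.5, so 172 per arm.

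**Compliance.** No assumed rates are needed. The outcome is the number of unused study medications. If completing the full course is read literally, a member of the per-protocol set has essentially nothing left over, and the arm difference in that set is about zero whatever happened in the trial. If completion is later given a looser threshold, the count in the set is not exactly zero but is still cut off at that threshold in both arms. Either way the comparison says little about compliance.

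**Adverse events.** Let *a* be the proportion of randomised patients in an arm with any adverse event and *s* the proportion who stopped because of one. If those are the only exclusions, the proportion with an event in the per-protocol set is (*a* − *s*) / (1 − *s*). The article gives neither *a* nor *s*; the values below are assumptions chosen to show the range.

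| Any event, dual / mono | Stopped for an event, dual / mono | Difference, all randomised | Per-protocol, dual / mono | Difference, per-protocol |
|---|---|---|---|---|
| 25% / 18% | 8% / 4% | 7.0 points | 18.5% / 14.6% | 3.9 points |
| 25% / 18% | 5% / 5% | 7.0 points | 21.1% / 13.7% | 7.4 points |
| 25% / 18% | 3% / 5% | 7.0 points | 22.7% / 13.7% | 9.0 points |
| 30% / 20% | 12% / 3% | 10.0 points | 20.5% / 17.5% | 2.9 points |

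First row: (0.25 − 0.08)/0.92 = 18.5% and (0.18 − 0.04)/0.96 = 14.6%. The per-protocol difference shrinks when more patients stop on dual therapy and widens when more stop on monotherapy.

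**Effect on the planned test.** Take the 12.5-point margin as applying to adverse events and use the normal approximation. The chance of concluding that monotherapy is non-inferior is Φ((0.125 + *d*)/SE − 1.96), where *d* is dual minus mono.

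- 25% / 18% with 8% / 4% stopping. All randomised, 172 per arm: SE 0.0441, 0.195/0.0441 = 4.42, chance 99%. Per-protocol, about 158 and 165 patients: SE 0.0413, 0.164/0.0413 = 3.97, chance 98%.
- 30% / 20% with 12% / 3% stopping. All randomised: SE 0.0464, 0.225/0.0464 = 4.85, chance 99.8%. Per-protocol, about 151 and 167 patients: SE 0.0441, 0.154/0.0441 = 3.50, chance 94%.

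The estimate can move a good deal. The conclusion of the planned test hardly moves.

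**Effect of the both-sets rule.** Both sets must exclude the margin. Where the per-protocol comparison is near zero by construction, as for compliance, the joint decision is in effect the ITT decision. Where it is biased, as it can be for adverse events, it can at most withhold a claim that ITT would support. It cannot create one that ITT does not support.

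**The case against.** The strongest reply has four parts.

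1. **No single sentence says that compliance or adverse events are tested per-protocol.** The both-sets rule speaks of one margin, and the only margin in the article is tied to treatment success and to a difference of proportions. A tablet count does not fit it as written, so the authors probably had efficacy in mind. That is plausible as to intent. But the sample size section extends the non-inferiority assessment to the secondary outcomes in so many words, and Data analysis does not narrow it. The plain reading is over-broad.
2. **ITT runs alongside and must also pass.** This stands and sets the severity. A reader might infer that adverse events leading to discontinuation vanish from the trial, or that non-inferiority on compliance could be declared by default. The documents support neither: ITT keeps every randomised patient, the sections under Safety reporting record all events with no per-protocol restriction, and a per-protocol pass is not enough alone.
3. **The adverse-event rates are invented and the direction is unknown.** This also stands. A reader might infer that the per-protocol set understates the tolerability advantage of monotherapy. That needs more stopping on dual therapy, which the article does not state; the third row of the table goes the other way. A large loss of power can be shown only with a test of whether the difference is zero, and the plan uses a one-sided non-inferiority interval.
4. **Safety sets and completion thresholds belong in the analysis plan.** Agreed, and their absence is not the point here. The point is a rule that is stated, and stated too widely. An analysis plan that exempted these outcomes would have to depart from it.

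**Conclusion.** The point holds as a minor one. Taken together, the two sections put compliance and adverse events into a per-protocol comparison whose membership depends on those same outcomes. For compliance the comparison is close to uninformative; it is exactly so only if completion is read literally. For adverse events it is open to bias of unknown sign and size: a 7.0-point difference became anything from 3.9 to 9.0 points under the assumed stopping rates, and a 10.0-point difference became 2.9 in the most lopsided case.

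The harm is a misleading per-protocol result and a second condition that adds nothing valid for these two outcomes. The primary conclusion, the sample size and data collection are unaffected, and no false non-inferiority claim results.

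**What to change.** In Data analysis, state that the per-protocol analysis and the requirement that both sets exclude the margin apply to the efficacy outcomes only. Add that compliance and adverse events are compared without excluding patients who stopped early: compliance in all randomised patients with a tablet count, and adverse events in all treated patients. The detailed definition of the safety set can stay with the analysis plan.

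The cost is one or two sentences, with no new data and no change to the 172 per arm. Trial status says that enrolment has not started, so the change can be made before any data exist.
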